### Blinding

Screening of windows and doors will not be blinded as it is difficult to conceal them. However, we will follow the World Health Organization 2015 [34] guideline in blinding other activities. The blood films will be read by microscopists blinded to the identity and intervention status of the subjects. Mosquito collection will be made by using standard CDC light traps thereby avoiding the potential bias that could be introduced by the fieldworkers to collect specimens. Mosquito identification will be made by different technicians who will not know the trap location.

### Interventions

#### Long-lasting insecticidal nets

DuraNet® (Shobikaa Impex pvt Ltd., Karur, Tamil Nadu 639,006, India) will be provided to all households (except control arm) at the rate of one bed net for two people following the NMCP and as per WHO recommended universal net coverage [1, 39]. The nets will be provided by NMCP district office and will be distributed to study households in the first week of July 2020. All study participants will receive new LLINs free of charge at the beginning of the intervention regardless of the previous ownership, with householders maintaining their existing nets at the time of distribution.

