**Methods:**

A four-armed household, cluster-randomized, controlled study will be conducted to assess the combined impact of HS, LLINs and push-pull agricultural technology (PPT) against clinical malaria in children in Ethiopia. The unit of randomization will be the household, which includes a house and its occupants. A total of 838 households will be enrolled in this study. In this trial 246 households will receive LLINs and HS, 250 will receive LLINs, HS and PPT, 175 households will receive LLINs and PPT. The remaining 167 houses which receive LLINs only will be used as control. One child aged ≤14 years will be enrolled per household in each treatment and followed for clinical malaria using active case detection to estimate malaria incidence for two malaria transmission seasons.

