**Fig. 1 Fig1:**
[figure not shown]
Flow chart of the study

In this study, a total of 167, 246, 250 and 175 houses will be included in four different treatments, treatment 1 (control, LLINs only), treatment 2 (LLINs and HS), treatment 3 (LLINs, HS and PPT) and treatment 4 (LLINs and PPT), respectively. The differences in sample size across arms is due to differences in number of households within each sub-village. To full fill the total sample size, we did the random selection based on population size of each sub-village. Census of children under 14, and above 14 years of age will be made in all 838 households selected. One child will be randomly selected from each house for annual malaria parasite survey. In addition to the annual parasite screening survey, monthly follow up will be implemented in all households to monitor clinical malaria by health extension workers. If a child moves or quits the study, we will replace the child from the same house. In instances where the whole family leaves the area, we will document them as lost to follow up.

The selected children will be checked up every month for clinical symptoms of malaria infection, splenomegaly, and development of anaemia. Blood test will be conducted if the child develops clinical symptoms. The child will also be surveyed at the beginning and end of each transmission season to estimate the prevalence of *Plasmodium species* infection, parasite density, and the prevalence of anaemia. Collections will be made from both indoor and outdoor settings.

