#### Push-pull technology

Push pull technology is a biological method of controlling pests of cereals: stem borer and striga. It is a novel pest control method in which a repellent intercrop and attractant trap plant is used simultaneously. It has three components which include the push, the pull, and the intercropped plant. The push component refers to desmodium plant, a.k.a. *Desmodium uncinatum*. The pull component refers to the brachiaria grass, *Brachiaria cv mulato,* which is usually planted at the periphery of the plot and the intercropped plant which is our target plant to be protected (Maize or Sorghum). While the desmodium is rich in protein, the brachiaria is rich in carbohydrate, which will serve as an important source of animal feed. The detail application of PPT is described elsewhere [40]. The desmodium plant releases a semiochemical that repels stemborer moths (push), and attracts their natural enemies, while brachiaria grass attracts them (pull). In addition to repelling the stem borer pests, desmodium is very effective in suppressing striga weed while improving soil fertility through nitrogen fixation and improved organic matter content. On the other hand, both plants provide high-value animal fodder, contributing to improved milk production and keep the health of the livestock [28, 41]. Both plants are proved to be drought resistant and can be used as source of animal feed in areas where rain is limited. According to a standard protocol developed by ICIPE for PPT application, a plot of any size can be used to implement the technology. A typical PPT plot is usually 25 by 25-m size. The brachiaria plants are sowed in three rows around the perimeter of the plot and separated by 75 cm width each other. The desmodium plant is sowed in alternate manner with the crop plant (maize or sorghum) [28].

Thus, as part of the intervention training will be provided to selected farmers on the concept of PPT and how to use it. These include plot preparation, sowing, establishing, managing, animal feed preparation and seed harvesting. A total of 425 farmers who successfully completed the training and who been selected to house screening treatment will be provided PPT plant seeds namely Mulato II Hybrid Brachiaria, (3 kg/ha, Barenbrug, [name]) and *Desmodium intortum* 3-5 kg/Ha from the same company. The amount of Kg provided to each farmer will be decided on the size of plot made ready by the farmer.

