## Discussion

Countries and inter-state actors who work in public health sectors are running out of options to contain vectors of malaria vectors as existing interventions become less effective due to growing insecticide resistance [4] and adaptive behavioral shift of vector mosquitoes to evade the interventions [50]. Thus, all options including research for novel vector control interventions [51], combination of existing strategies (e.g. combination of LLINs and IRS, [52] and supplementing them with auxiliary strategies e.g. combination of LLINs and HS, [14] are being tried as part of the ongoing research and innovation in the field of vector control. In addition, a recent modelling study conducted by Kassie et al. (2020) [53] showed that integrated interventions aimed at relaxing the constraints of multiple health problems (animal-human-plant health) are more effective in improving the overall welfare of humans as compared to the stand alone interventions. Thus, in this study we aim to test and assess the combined effect of 1) LLINs and HS 2) LLINs, HS and PPT and 3) LLINs and PPT. Households that receive LLINs alone will be used as control.

Screening houses for the purpose of excluding mosquito vectors into residential structures is well established practice in Europe [54], America [55] and some parts of tropics [5] however, these experiences were given less emphasis in Africa as main stay vector control intervention (LLINs and IRS) predominated the vector control arena. A specific design of the house (e.g. thatched roof, Iron sheet cover, closed eve, open eve) can play critical role in increasing or decreasing the odds of malaria infection [9] and mosquito density per capita or per house [36, 56,  57]. In addition to alleviating malaria, the introduction of house screening intervention in houses has resulted in reduced infection of other vector borne diseases such as dengue, leishmaniasis, yellow fever and Zika [58].

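### The net-delivery text contradicts itself and the definition of the control arm; the PPT seed sentence conflicts with arm 4

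*Protocol article*

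**What the plan says.** **Arm definitions.** The text under Fig. 1 (Study flow chart) states that "a total of 167, 246, 250 and 175 houses will be included in four different treatments, treatment 1 (control, LLINs only", and closes the list with "treatment 3 (LLINs, HS and PPT) and treatment 4 (LLINs and PPT), respectively". Arm 2, with 246 houses, is LLINs plus HS. The Abstract says "The remaining 167 houses which receive LLINs only will be used as control", and the Discussion repeats "Households that receive LLINs alone will be used as control". The General objective also names LLINs alone as the comparator.

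**Net delivery.** The section Long-lasting insecticidal nets makes two statements. Its first sentence says the nets "will be provided to all households (except control arm) at the rate of one bed net for two people". Its last says "All study participants will receive new LLINs free of charge at the beginning of the intervention regardless of the previous ownership", and adds that households keep the nets they already have.

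**Seed delivery.** The section Push-pull technology says: "A total of 425 farmers who successfully completed the training and who been selected to house screening treatment will be provided PPT plant seeds".

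**The concern.** The trial asks what HS and PPT add to LLINs. That needs net provision to be the same in every arm, so that an intervention arm differs from control only by HS, PPT or both. One sentence on net delivery breaks this condition and another in the same section restores it, so a reader cannot tell from the article which was planned.

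If control households received no new nets, every comparison with control would carry the effect of new nets as well. A benefit from new nets would act in the direction of the hypothesised benefit of HS and PPT. The mixed-effects Poisson model in Malaria incidence data analysis could not separate the two, because new-net provision would coincide exactly with being in any arm other than control.

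The seed sentence raises a lesser problem of the same kind. Its condition, selection for screening, does not fit arm 4, which is defined by PPT without screening.

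**Working it through.** No power or variance formula applies. The check counts households under each statement and then asks what each contrast would contain.

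**Inputs** (Study flow chart): arm 1 (control, LLINs) 167; arm 2 (LLINs + HS) 246; arm 3 (LLINs + HS + PPT) 250; arm 4 (LLINs + PPT) 175.

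**The article's own totals**
- All arms: 167 + 246 + 250 + 175 = 838, as stated.
- PPT arms 3 + 4: 250 + 175 = 425, exactly the number of farmers stated in Push-pull technology.
- Screened arms 2 + 3: 246 + 250 = 496, consistent with the round 500 in House screening.

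**Nets**

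| Statement | Households given new nets |
|---|---|
| First sentence (control excepted) | 838 − 167 = 671 |
| Last sentence (all participants) | 838 |

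The statements differ by the 167 control households, 167/838 = 19.9% of the trial.

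**Seed**

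| Reading | Farmers given seed |
|---|---|
| Allocated to PPT and to screening | 250 (arm 3 only) |
| Stated count | 425 = 250 + 175 (arms 3 and 4) |

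The gap is 425 − 250 = 175, exactly arm 4. It is 175/425 = 41% of the PPT households and 175/838 = 20.9% of the trial. The two conflicts together concern 167 + 175 = 342 households, 342/838 = 40.8%.

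**Content of the contrasts if the net exclusion were followed.** Write *n*, *h* and *p* for the log rate ratios of new nets, HS and PPT, and *i* for any interaction of HS with PPT. Take arm 4 as having received PPT.
- Arm 2 vs arm 1: *n* + *h*
- Arm 4 vs arm 1: *n* + *p*
- Arm 3 vs arm 1: *n* + *h* + *p* + *i*
- Arm 3 vs arm 4: *h* + *i*, with *n* and *p* cancelling

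Every contrast with control contains *n*. Arm 3 versus arm 4 does not. It gives the effect of HS on top of nets and PPT, which equals the effect of HS over nets alone only if *i* = 0. If arm 4 had received no PPT, arm 3 versus arm 4 would be *h* + *p* + *i* and would no longer isolate HS.

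**The case against.** The strongest reply is that the weight of the text favours the arm definitions. Four places describe control as LLINs only, and the last sentence of the net section gives new nets to everyone; a single parenthesis says otherwise. The seed sentence carries its own correction, since its count of 425 includes all of arm 4, so the screening condition is probably a slip of wording.

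Much of this stands. A reader might infer that arms 1 and 4 will not receive what defines them. The documents do not support that: each withholding phrase is opposed by other text, and for seed by the number in the same sentence. Nor does any sentence say that control households in particular rely on old nets; the remark about keeping existing nets is made of all participants.

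A reader might also infer that farmers who do not complete training are dropped from the analysis. The seed sentence makes supply depend on training but states no such exclusion, and 425 is the full allocated number. The replacement rule in Malaria incidence data analysis is a separate matter.

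The size of any bias cannot be given either. The documents contain no figure for the effect of new nets over existing ones, and an assumed figure would only return itself as the bias.

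The net contradiction survives these replies. The exclusion is explicit, the opposing sentence is equally explicit, and a trial with new nets in arms 2 to 4 and existing nets in control would be coherent on paper. Likely intent does not tell the reader what was delivered.

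**Conclusion.** The concern holds as a contradiction in the delivery text. For nets, the article gives both 671 and 838 recipient households, and the 671 conflicts with the stated comparator. If the exclusion was followed, all three contrasts with the 167 controls are confounded with new-net provision and do not answer the general objective. If it was not, the sentence is wrong but the design is intact. The article alone cannot say which.

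The seed sentence is a secondary wording conflict affecting the 175 households of arm 4. Taken alone it would be minor. It gains weight because the only direct HS contrast between two PPT arms, arm 3 versus arm 4, depends on arm 4 having received PPT.

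The conclusion rests on the stated arm sizes and definitions and on no outside figure.

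**What to change.** 1. Reconcile the first sentence of Long-lasting insecticidal nets with the last sentence of that section and with the control definition in the Abstract, General objective, Study flow chart and Discussion.
2. Reconcile the seed sentence in Push-pull technology with the 250 + 175 PPT households of the Study flow chart, so that each arm's delivery text matches its definition.
3. Verify and report receipt of new nets and of PPT seed by arm.
4. If new-net provision did differ from control, label all contrasts with control as including new nets. Provided arm 4 did receive PPT, take the HS effect from arm 3 versus arm 4, and state that this is HS in the presence of PPT.

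The cost is two corrected sentences and a check of receipt. The questionnaire already covers LLIN ownership and use (Data collection methods), and net presence is observed at mosquito-sampling visits (Socio-economic data collection methods). The check would need to tell new nets from nets already owned. The article does not say what distribution records exist, so the effort for that part is not known.

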#### House screening

The house screening work will be undertaken by pre-trained artisans of about 4 to 5 people to be recruited from the study area. The training will be done by an in-country contractor familiar with screening of houses. The screening of 500 houses is expected to take about 2 months. Household owners will be trained on the care needed to keep the screens intact and effective and avoid activities that could result into making holes in the mesh or cause the screen to slide and create spaces that could allow mosquito entries into the houses. Other routine procedures to be used to reduce mosquito entry into houses such as closing windows and doors early will be emphasized and adherence to this practice monitored passively by the study team. As part of the intervention all the windows, doors and eaves will be screened using polyethylene material (POLYTEX INTERNATIONAL (UK) LIMITED, [name]).

#### Push-pull technology

Push pull technology is a biological method of controlling pests of cereals: stem borer and striga. It is a novel pest control method in which a repellent intercrop and attractant trap plant is used simultaneously. It has three components which include the push, the pull, and the intercropped plant. The push component refers to desmodium plant, a.k.a. *Desmodium uncinatum*. The pull component refers to the brachiaria grass, *Brachiaria cv mulato,* which is usually planted at the periphery of the plot and the intercropped plant which is our target plant to be protected (Maize or Sorghum). While the desmodium is rich in protein, the brachiaria is rich in carbohydrate, which will serve as an important source of animal feed. The detail application of PPT is described elsewhere [40]. The desmodium plant releases a semiochemical that repels stemborer moths (push), and attracts their natural enemies, while brachiaria grass attracts them (pull). In addition to repelling the stem borer pests, desmodium is very effective in suppressing striga weed while improving soil fertility through nitrogen fixation and improved organic matter content. On the other hand, both plants provide high-value animal fodder, contributing to improved milk production and keep the health of the livestock [28, 41]. Both plants are proved to be drought resistant and can be used as source of animal feed in areas where rain is limited. According to a standard protocol developed by ICIPE for PPT application, a plot of any size can be used to implement the technology. A typical PPT plot is usually 25 by 25-m size. The brachiaria plants are sowed in three rows around the perimeter of the plot and separated by 75 cm width each other. The desmodium plant is sowed in alternate manner with the crop plant (maize or sorghum) [28].

Thus, as part of the intervention training will be provided to selected farmers on the concept of PPT and how to use it. These include plot preparation, sowing, establishing, managing, animal feed preparation and seed harvesting. A total of 425 farmers who successfully completed the training and who been selected to house screening treatment will be provided PPT plant seeds namely Mulato II Hybrid Brachiaria, (3 kg/ha, Barenbrug, [name]) and *Desmodium intortum* 3-5 kg/Ha from the same company. The amount of Kg provided to each farmer will be decided on the size of plot made ready by the farmer.

#### Risks and harms

There is no risk of any infection as we do this study, however, finger pricking for blood test is usually with mild pain and discomfort.

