### Study endpoints/outcomes

#### Clinical evaluations

The main outcomes of the clinical study will be the malaria incidence, splenomegaly, and anaemia. Thus, the baseline clinical survey of all study children will take place between Sept and Oct 2020 to determine the clinical parameters. As part of the follow up, starting from Nov 2020, trained health extension workers will visit the house of each child and take data of clinical symptoms, temperature, and splenomegaly (sign of spleen enlargement). While monthly follow up of the child continues throughout the 2 years of study period (Sept 2020 to Dec 2022) for documentation of any malaria incidence, blood testing of the entire cohort of the study children will be repeated at the end of each rainy season (Sept/Oct 2021) and Sept/Oct 2022). In between the annual clinical surveys (i.e., at the time of monthly follow up), blood testing will be done only to children who develop fever to minimize community fatigue development. Temperature measurement, RDT testing, blood haemoglobin measurement, blood sample collection for microscopy will be conducted by a licensed laboratory professional following the WHO guideline [44].

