### Safety and monitoring

#### Safety evaluations

House to house visit, children follow up and RDT testing during monthly follow up period will be conducted by the trained health extension workers (HEWs). Yearly blood sample collection and processing will be handled by professional. Blood samples for RDTs, microscopic examination and Haemoglobin test measurements will be collected using aseptically disposable lancets. Positive, cases found during the monthly follow up will be treated by the HEWs according to the national guidelines [40] and any complications that could potentially develop in to series adverse effect (SAE) on participants will be referred to the nearby health center or hospital and reported to the principal investigator.

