Push pull technology on the other hand is a semiochemical based intervention in which two plant species are being used in integrated approach with primary objective of increasing the quality and quantity of crop yield per unit area. It is developed at ICIPE research center, Kenya, in collaboration with Rothamsted research center UK and scaled up throughout Africa to support smallholder farmers [59]. The strategy is non-synthetic chemical, and it involves the intercropping of cereal crops with a forage legume, desmodium, and planting Napier grass as a border crop [27]. In this approach the *Desmodium intortum* plant releases the semiochemical which repels stem borer moths, and attracts their natural enemies, while Napier grass (now replaced by *Bracharia mulatotu*-II) attracts the pest. In addition, the *Desmodium* plant can effectively suppress striga weeds and improve soil fertility through nitrogen fixation. Both plants provide animal fodder thereby increasing the health and productivity of livestock. Commercialization of these companion crops can be used as a source of income generation through seed production. By integrating the push-pull technology and malaria vector control interventions, we hypothesize that the PPT will improve the livelihood of farmers through increased production and productivity thereby the synergy of the technologies contributing to improved overall life standard including the fight against malaria.

We expect some mild risks arising from this study. Screening of windows and doors may lead to reduced aeration in houses which may result in respiratory infection of children as it was hypothesized in similar studies conducted in The Gambia [14]. Routine monitoring of respiratory infections will be made on households enrolled in the study to document if there exists any incidence. In case of encountering any such infections, children will be referred to nearby health center for immediate treatment. We hypothesize that there would be significant reduction in mosquitoes entering houses due to screening which may lead to complacence in using bed nets. As part of routine monitoring and house-to-house visit, we will make sure that people continue to use LLINs as usual and educate them that HS is not a stand-alone intervention.

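### The risk section rules out any infection risk, but the Discussion names a possible respiratory infection risk from screening, and the monitoring promised there is not carried into the visit or safety procedures

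*Protocol article*

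**What the plan says.** The Risks and harms section, placed under Interventions after the descriptions of nets, screening and push-pull technology, is a single sentence. It states "There is no risk of any infection as we do this study" and then mentions mild pain from the finger prick. No other harm is listed.

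The Discussion takes a different position. It opens the topic with "We expect some mild risks arising from this study" and continues: "Screening of windows and doors may lead to reduced aeration in houses which may result in respiratory infection of children". It attributes this hypothesis to similar studies elsewhere. It then makes two commitments: "Routine monitoring of respiratory infections will be made on households enrolled in the study to document if there exists any incidence", and, where an infection is found, "children will be referred to nearby health center for immediate treatment".

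Three sections describe what is done at follow-up visits. The text under Study flow chart lists malaria symptoms, spleen enlargement and anaemia. Epidemiological data collection methods describes temperature, fever history and rapid diagnostic testing (RDT). Clinical evaluations says that health extension workers will "take data of clinical symptoms, temperature, and splenomegaly".

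Safety evaluations describes the visits, the blood sampling and what follows a positive test: "Positive, cases found during the monthly follow up will be treated by the HEWs". The same sentence adds that complications in participants that could become serious are referred and reported to the principal investigator. Respiratory infection is not named in any of these four sections.

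**The concern.** There are two linked problems.

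First, the one section devoted to harms denies any infection risk, while another part of the same article names one. A reader who consults only the harms section, as an ethics committee or a later systematic reviewer may, would come away with the wrong account.

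Second, the safeguard against that risk is stated only in the Discussion. Field staff work from the procedures. If the procedures do not say that respiratory infection is looked for, whether it is recorded depends on how each worker reads general phrases about symptoms and complications. Screening is not blinded, so recording that is left to discretion could also differ between screened and unscreened houses. The Conclusion says the findings will be used by national malaria control programmes. Such programmes would want an interpretable statement on this possible harm alongside the benefit.

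**Working it through.** There is no figure to reproduce; the point rests on comparing the sections of the protocol article.

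**Step 1. Are the two risk statements compatible?**

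| Section | Infection risk | Harm named |
|---|---|---|
| Risks and harms | None of any kind | Finger-prick discomfort |
| Discussion | Possible, through reduced aeration after screening | Respiratory infection in children |

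The first statement has no qualifier: it is not limited to blood sampling or to malaria, and it speaks of the study as a whole. The second is tentative, since both of its links are put as possibilities. A possible infection risk is still incompatible with the statement that there is none.

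**Step 2. Does the monitoring promise reach the procedures?**

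| Section | What it covers | Respiratory item named? |
|---|---|---|
| Study flow chart | Malaria symptoms, spleen, anaemia | No |
| Epidemiological data collection methods | Temperature, fever history, RDT, blood spots, anaemia, spleen | No |
| Clinical evaluations | Clinical symptoms in general, temperature, spleen | No |
| Safety evaluations | Visits, sampling, treatment of positives, complications in general | No |
| Discussion | Respiratory infections in enrolled households, with referral | Yes |

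The promise is found only in the last row.

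**Step 3. Do the procedures exclude respiratory infection, or are they unclear?** They are unclear. Clinical evaluations speaks of clinical symptoms without restriction, but Study flow chart ties the monthly symptoms to malaria. Safety evaluations refers to complications in participants generally, but does so in a sentence that begins with malaria-positive cases. A broad and a narrow reading are both open.

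**Step 4. Would uniform recording allow a comparison?** The arm sizes under Study flow chart give 246 + 250 = 496 households with screening (treatments 2 and 3) and 167 + 175 = 342 without (treatments 1 and 4); 496 + 342 = 838, the stated total. The trial therefore already contains screened and unscreened arms, followed by the same monthly visits. One uniformly recorded item could be summarised between them. These counts show only that the comparison is available; they say nothing about the size of the risk.

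**The case against.** The strongest reply is that the protocol has already dealt with this. The Discussion itself plans monitoring, documentation and referral. It does so for enrolled households, which covers all four arms, and does not make it depend on an RDT result. It also mentions routine monitoring together with house-to-house visits, which suggests that the same visits are meant. The sentence in Risks and harms may have been intended for blood sampling only, since it goes straight on to the finger prick. An article may also leave the detailed visit form to the full protocol.

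Much of this stands, and it rules out several stronger readings:

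- A reader might infer that the protocol expects screening to cause infection. It expects mild risks and says that infection may result.
- A reader might infer that a child with a respiratory infection and a negative RDT falls outside every stated route. The Discussion states a route, and the general wording elsewhere could include such a child.
- A reader might take Safety evaluations to cover only malaria-positive children. Its clause on complications refers to participants.
- A reader might conclude that families are told there is no infection risk. Informed consent says that the consent form covers risks, but the form is a separate file and is not shown.
- A reader might want diversion of mosquitoes to unscreened houses added as an undisclosed harm. Study flow chart names it and limits coverage to 5% of houses per village.
- A reader might multiply arm sizes by the number of monthly visits to give the gap a size. That counts occasions for recording; it measures neither risk nor bias.

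The reply does not remove the contradiction. The narrower reading of Risks and harms is possible, but its wording is unqualified. Nor is the second part just a complaint about a missing form: the article does list visit content and a safety route in four places, and its own monitoring promise is in none of them.

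**Conclusion.** The point holds as a minor safety matter. Risks and harms is wrong as written when set against the Discussion, and the two must be reconciled. The respiratory monitoring is promised but not placed in the procedures, so whether it would be captured is ambiguous; it is not shown to be absent. The primary malaria analysis and the sample size are unaffected. The risk cannot be quantified, because the documents give no respiratory infection rate.

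The conclusion assumes that the article's visit and safety sections reflect what field staff are asked to do. If the full protocol or the visit forms already contain a respiratory item for all arms, the second part reduces to an editorial alignment. The first part stands either way.

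**What to change.** 1. Revise Risks and harms so that it names the possible respiratory risk described in the Discussion and no longer denies every infection risk. Check that the consent form (not shown) says the same.
2. State the monitoring already promised in the Discussion within Clinical evaluations and Safety evaluations. Make it one identically worded item, asked at the existing monthly visits in all four arms whatever the RDT result.
3. Summarise that item descriptively for the screened arms (treatments 2 and 3) against the unscreened arms (treatments 1 and 4).

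The cost is some revised text, one item on an existing visit and one descriptive summary. The downside is a slightly longer visit. No change to the randomisation, sample size or malaria analysis is needed.
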